**LIST OF ABBREVIATIONS AND RELEVANT DEFINITIONS**

| **ABR** | **ABR form, General Assessment and Registration form, is the application form that is required for submission to the accredited Ethics Committee (In Dutch, ABR = Algemene Beoordeling en Registratie)** |
| --- | --- |
| **AE** | **Adverse Event** |
| **AR** | **Adverse Reaction** |
| **CA** | **Competent Authority** |
| **CCMO** | **Central Committee on Research Involving Human Subjects; in Dutch: Centrale Commissie Mensgebonden Onderzoek** |
| **CV** | **Curriculum Vitae** |
| **DSMB** | **Data Safety Monitoring Board** |
| **EU** | **European Union** |
| **EudraCT** | **European drug regulatory affairs Clinical Trials** |
| **GCP** | **Good Clinical Practice** |
| **IB** | **Investigator’s Brochure** |
| **IC** | **Informed Consent** |
| **IMP** | **Investigational Medicinal Product** |
| **IMPD** | **Investigational Medicinal Product Dossier** |
| **METC** | **Medical research ethics committee (MREC); in Dutch: medisch ethische toetsing commissie (METC)** |
| **(S)AE** | **(Serious) Adverse Event** |
| **SPC** | **Summary of Product Characteristics (in Dutch: officiële productinfomatie IB1-tekst)** |
| **Sponsor** | **The sponsor is the party that commissions the organisation or performance of the research, for example a pharmaceutical**  **company, academic hospital, scientific organisation or investigator. A party that provides funding for a study but does not commission it is not regarded as the sponsor, but referred to as a subsidising party.** |
| **SUSAR** | **Suspected Unexpected Serious Adverse Reaction** |
| **Wbp** | **Personal Data Protection Act (in Dutch: Wet Bescherming Persoonsgevens)** |
| **WMO** | **Medical Research Involving Human Subjects Act (in Dutch: Wet Medisch-wetenschappelijk Onderzoek met Mensen** |

**SUMMARY**

**Rationale:** Anxiety disorders are highly prevalent disorders. They cause considerable human suffering and substantial societal and economic costs, estimated to be more than 1 billion euros annually. A possible way to make treatment more cost-effective lies in *blended care*. This type of treatment combines elements of both online and face-to-face cognitive behavioral therapy (CBT).

**Objective**: In this RCT, we will examine the health care efficiency of blended care treatment for patients with a severe anxiety disorder in outpatient specialized (secondary) mental health care. The results of this cost-effectiveness study will provide 1) an insight into the health-economical outcomes of ‘blended treatment’ 2) an indication whether blended treatment will add value when it is implemented in routine specialized mental healthcare settings, and 3) a good indication whether blended treatment for severe anxiety disorders in routine practice is advisable and feasible from the perspective of different stakeholders including patients, mental health service providers and health insurers.

**Study design:** A randomized controlled trial with two parallel conditions in which blended CBT will be compared to face tot face CBT treatment as usual (CBT-TAU), for anxiety disorders

**Study population:** Patients (≥18 years old) with a diagnosis of a severe anxiety disorder (panic disorder with or without agoraphobia, social phobia, and generalized anxiety disorder) who were referred to outpatient specialized mental health care services.

**Intervention**: The blended treatment consists of 12 to 20 CBT sessions, alternating between 6 to 10 face-to-face and 6 to 10 Internet sessions. Treatment as usual will consist of 12 to 20 face-to-face CBT sessions on average (CBT-TAU). (The number of sessions depends on the type of anxiety treatment).

**Main study parameters/endpoints:** The health-economic analyses combine clinical outcomes with cost estimates. Primary clinical outcomes are 1) recovery from*,* 2) changes in anxiety symptom severity, 3) quality-adjusted life years (QALY’s), and 4) health-related quality of life. Cost estimates are 1) costs of offering the treatments and 2) patients’ out-of-pocket costs (non-medical), such as the costs of travelling to the health services and the patients’ time costs of travelling, waiting and receiving treatment. Furthermore cost estimates include 3) costs stemming from health care uptake, including costs of medication and 4) costs stemming from productivity losses due to absenteeism and reduced efficiency while at work (presenteeism).

**Nature and extent of the burden and risks associated with participation, benefit and group relatedness:** Blended treatment is not considered to add risks to the treatment, compared to treatment as usual. The questionnaires can be considered a slight burden for patients in both conditions.

# INTRODUCTION AND RATIONALE

Anxiety disorders (1 year prevalence 10,1%, incidence 3,1%) are severe psychiatric disorders associated with a poor quality of life and substantial economic ramifications (Graaf R de, 2010; RIVM, 2013; Smit et al., 2006). In the Netherlands, the annual healthcare costs associated with anxiety disorders are estimated at €286 million, 45% (€128 million) of which is spent on secondary mental health care, to treat patients with more severe anxiety disorders. Costs due to absenteeism in anxiety disorders are estimated at €998 million per year (RIVM, 2013), exceeding those of depression which are estimated at €467.4 million (GGZNederland, 2010; RIVM, 2013; Smit et al., 2006) In 2007, the total disease burden caused by anxiety disorders was 202,000 DALY’s in the Netherlands, being third in the top ten list of medical disorders and having a higher cost impact than depression, diabetes or lung cancer (RIVM, 2013).

For the above reasons it is of paramount importance to deliver appropriate and efficient treatment in severe anxiety disorders to decrease the public health impact of these disorders. Anxiety disorders can be treated effectively with cognitive-behavioural therapies (CBT), whether or not combined with pharmacotherapy. CBT is regarded as treatment as usual (TAU) and recommended in national and international treatment guidelines (NICE; www.ggzrichtlijnen.nl). It has been shown that anxiety disorder patients in the Netherlands have a preference for non-pharmacological treatment. In addition, compared with pharmacotherapy, patients who achieve full remission after treatment with CBT are less likely to relapse when treatment has stopped (Bruce et al., 2005). However, less than half of the patients with anxiety disorders receives appropriate treatment (Bijl et al., 2003), due to anxiety related avoidance behaviour, stigmatisation, costs, and a perceived lack of availability of appropriate treatments (Reger and Gahm, 2009).

Internet interventions, especially internet-based cognitive behavioral treatment (iCBT), are seen as an important strategy for lowering the costs of the treatment of common mental health disorders (e.g. unipolar depression and anxiety disorders).

Internet based cognitive behavioural therapy programmes (iCBT) have been developed for most common anxiety disorders like panic disorder with or without agoraphobia, social phobia and generalized anxiety disorder, which have proven to be at least equally effective as face-to-face psychotherapy. Another advantage of iCBT is that it requires less therapist time and as a consequence is expected to be less costly than conventional CBT.

Studies show that anxiety treatment delivered via Internet is more effective than non-intervening and that it can be as effective as face-to-face treatment (Andersson et al., 2014; Andrews et al., 2010; Cuijpers et al., 2009; Haug et al., 2012; Lewis et al., 2012; Mayo-Wilson and Montgomery, 2013; Reger and Gahm, 2009; Spek et al., 2007). Importantly, studies investigating the cost-effectiveness of Internet-based depression and anxiety treatments suggest that these may also be more cost-effective than face-to-face treatment, but the number of studies is still scarce (e.g., (Gerhards et al., 2010; Hedman et al., 2014; Hedman et al., 2012; Lokkerbol et al., 2014; Nordgren et al., 2014; Smit et al., 2011; Tyrer et al., 2014; Warmerdam et al., 2010). Additionally, it should be noted that most study results are obtained among self-referred depressed individuals from the general population who participate in standalone Internet treatments (Riper, 2013).

Clinical and economical evaluations of treatment of anxiety via Internet among patients in routine primary care and specialized mental health care services are still scarce. A rather new treatment approach combines face-to-face treatment with Internet sessions into one integrated treatment. This is a so-called ‘blended’ treatment approach (Riper, 2013). Viewed from a cost-effectiveness perspective, blended treatment could possibly diminish the number of face-to-face contacts, increase self-management competencies of patients and thereby decrease the overall (direct) costs of depression treatment. This approach could also have a positive effect on waitlist periods, as therapists can take on more patients, reducing the number of patients that are waitlisted. Dutch mental health care organizations are ready to implement blended treatment, and they are motivated to do so by Dutch health policy makers and insurers (Bakker, 2013), because it is assumed that blended cognitive behavioural therapy (bCBT) and usual face-to-face CBT (CBT-TAU) are at least similarly clinically effective, and that bCBT can be offered at lesser costs. At present, however, little is known about the clinical and health-economic benefits of blended treatment.

In the current cost-effectiveness study, we will examine health care efficiency in a randomized controlled trial of bCBT vs. face-to-face CBT (CBT-TAU), among patients with a diagnosis of with a diagnosis of a severe anxiety disorder like panic disorder with or without agoraphobia, as social phobia or a generalized anxiety disorder. The proposed study is one of a series of projects in which we explore the potential of a ‘blended cognitive behavioral treatment‘ (bCBT) for anxiety and depression.

The study is funded through the healthcare efficiency funding program (Dutch: doelmatigheidsonderzoek) of the Netherlands Organization for Health Research and Development (ZonMw). In subprogram 2 of this funding program, ZonMw enables the investigation of health care efficiency of applied interventions.

# The results of this cost-effectiveness study will provide a) insight into the health-economical outcomes of ‘blended treatment’, b) indication whether blended treatment will add value when it is implemented in clinical settings, and c) insight in whether blended treatment for anxiety is advisable and feasible from the perspective of various stakeholders.2. OBJECTIVES

This cost-effectiveness study will compare blended cognitive behavioral treatment (bCBT) with standard face-to-face CBT (CBT-TAU) among patients with a diagnosis of an anxiety disorder referred to an outpatient specialized mental health care.

The main goal of the study is to explore the health-economic outcomes of bCBT in comparison to CBT-TAU, through cost-effectiveness analysis (CEA), cost-utility analysis (CUA) and a budget impact analysis (BIA), both from a societal and a healthcare perspective.

We assume that bCBT and CBT-TAU are similarly clinically effective, but that bCBT can be offered at lesser costs. Hence, we expect health-economic outcomes of bCBT to be favorable in comparison to those of CBT-TAU. If so, this would justify further large-scale evaluations and dissemination efforts.

# STUDY DESIGN

The study is a cost-effectiveness study, designed as a parallel-group randomized controlled trial (N = 156), in which participants are randomly allocated to either bCBT (n=78) or CBT-TAU (n=78). Participants are recruited in Dutch specialized mental healthcare centers (GGZInGeest, GGZAltrecht or GGZ Oost Brabant), large scale mental health service organizations, respectively in the Amsterdam, Utrecht and Noord-Brabant region.

# Measurements are taken at four fixed 6-10-week intervals (depending on the type of anxiety treatment); at baseline (T0), week 6-10, week 12-20 and at weeks 64-72 (52 weeks follow-up) (T1 – T3). The recruitment of participants aims to start April 2015 (first patient in; after Medical Ethics (METC) consent) and the inclusion ends at December 2016, and the follow up at December 2017. For detailed information on the sample size and power calculation, see the study protocol.

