# STUDY POPULATION

## Population (base)

## The study targets adults with a current severe anxiety disorder (panic disorder with or without agoraphobia, social phobia, and generalized anxiety disorder), who were referred to and enrolled in an outpatient treatment in specialized mental healthcare center of GGZ Altrecht, GGZ inGeest or GGZ Oost Brabant. The likelihood that the planned number of patients can be recruited from the defined source population is considered high. Recruitment will take place during a time span of 18 months (see flowchart). Recruitment will start at the outpatients departments of GGZingeest ‘De Nieuwe Valerius’, at both outpatient departments of GGZ Altrecht and GGZ Oost-Brabant location Oss. Based on the number of patients that were diagnosed with an anxiety disorder at GGZinGeest last year we would expect around 30 patients per month receiving treatment. We aim to include 8-10 patients per month in the current study. If after 6 months the number of included patients is less than 78 patients, the management of GGZ inGeest has agreed to add two more locations as recruitment sites for this study, yielding a total of approximately 800 patients from which to recruit the intended 156 study participants

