## Study procedures

Patients will be recruited within outpatient Anxiety Disorder departments of the participating Mental Health Care site(s) of GGZingeest, GGZ Altrecht and GGZ Oost-Brabant in the Netherlands. During their intake interview, all new patients indicate whether they are willing to participate in a study. All patients with a primary diagnosis of a severe anxiety disorder (panic disorder with or without agoraphobia, social phobia, and generalized anxiety disorder) who are willing to participate will be approached by the researchers by telephone and asked to participate in the study. Participants then receive a letter containing information on the study and the informed consent form (including a return envelope).

After a week, the researchers will contact the patient again. When the patient is willing to participate, a trained researcher then screens the patients with respect to the inclusion and exclusion criteria based on the SCID-I diagnosis and the patient’s demographic characteristics, such as age.

Patients who are not eligible to participate will be notified and remitted to regular treatment trajectories within the participating specialized mental health care center(s).

If patients are eligible to participate, written informed consent will be obtained. Subsequently, patients receive an email containing an invitation to fill in the online questionnaires. When the baseline measures are completed, patients are randomized to either bCBT or CBT-TAU. Treatment duration is 12-20 weeks in the bCBT group and 12-20 weeks in the CBT-TAU group. When necessary, additional treatments are allowed for all patients at any point of time during the study.

After 6-10, 12-20 and after 64-72 weeks (52 weeks follow-up), the patient is asked to complete a number of measures (see Table 1), which consist of a diagnostic interview (SCID-I and a set of online questionnaires).

At week 64-72 (52 weeks follow-up) the full SCID-I interview is administered to assess whether the anxiety disorder is present and to determine co-morbid disorders. The SCID-I can be administered via the telephone and face-to-face at a the mental health care location, depending on patient preference. A full SCID-I interview takes 60 minutes at most. Administering sections on anxiety disorders takes about 10 minutes.

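### The calendar ends follow-up about 52 weeks after inclusion closes, but the last assessment (T3) is due 64-72 weeks after baseline, so it is 12-20 weeks too short for the last recruits

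*Protocol*

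**What the plan says.** Protocol Section 3 (Study design) gives the calendar. On the start it says "The recruitment of participants aims to start April 2015", and on the end "the inclusion ends at December 2016, and the follow up at December 2017". The same paragraph puts the last assessment "at weeks 64-72 (52 weeks follow-up" weeks in brackets, counted from baseline.

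Section 8.3 (Study procedures) repeats the window: "After 6-10, 12-20 and after 64-72 weeks (52 weeks follow-up), the patient is asked to complete a number of measures". It also explains where the window comes from: "Treatment duration is 12-20 weeks in the bCBT group and 12-20 weeks in the CBT-TAU group". Weeks 64-72 appear again in the Figure 1 flowchart, Table 1, Section 10.2 and Section 12.1.

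Section 4.1 (Population) gives another recruitment period, "Recruitment will take place during a time span of 18 months (see flowchart"), and a rate: "We aim to include 8-10 patients per month in the current study".

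Table 1 lists the BAI, SCID-I, EQ-5D, SF-36 and TiC-P at T3 under primary outcomes. Section 10.1 uses costs at one-year follow-up. Section 12.5 defines the end of the study as the final visit of the final patient.

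**The concern.** The calendar appears to add one year to the end of inclusion and to leave out the treatment period that comes before the one-year follow-up. If so, the printed end date falls before T3 is due for anyone recruited late.

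T3 carries weight in this trial. It is the only assessment after the end of treatment, and in Table 1 it holds the only SCID-I after baseline (Sections 8.2 and 8.3 can be read as placing interviews at other visits too). It also closes the longest interval over which costs and utilities are measured: 52 of 64-72 weeks. A patient cut off before T3 would contribute nothing to the cost-effectiveness comparison after treatment ends. Because the length of the schedule depends on the type of anxiety treatment, a calendar cut-off would fall more often on patients with the longer schedule.

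**Working it through.** **Inputs.** Start of recruitment April 2015, end of inclusion December 2016, end of follow-up December 2017, T3 at weeks 64-72 (Section 3). Treatment 12-20 weeks (Section 8.3). Recruitment 18 months at 8-10 per month (Section 4.1). N = 156 (Section 3). Assumptions: recruitment opens on 1 April 2015, baseline is on the day of inclusion, and December means the last day of the month unless stated otherwise.

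**1. The T3 window reproduces.** 12 + 52 = 64 and 20 + 52 = 72. The window is therefore deliberate and not a misprint.

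**2. Time allowed against time needed.** From 31 December 2016 to 31 December 2017 is 365 days, or 52.1 weeks.
- Week 64: 31 December 2016 + 448 days = 24 March 2018. Shortfall 64 - 52.1 = 11.9 weeks.
- Week 72: 31 December 2016 + 504 days = 19 May 2018. Shortfall 72 - 52.1 = 19.9 weeks.

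Varying the day chosen within each December moves the shortfall between 7.6 weeks (1 December 2016 to 31 December 2017, week 64) and 24.1 weeks (31 December 2016 to 1 December 2017, week 72). It never reaches zero.

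**3. Last inclusion that still fits.** Counting back from 31 December 2017 gives 9 October 2016 for week 64 and 14 August 2016 for week 72.

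**4. The 18-month period.** April 2015 to December 2016 is 21 calendar months; 18 months would end on 30 September 2016. From that date week 64 is 22 December 2017, which just fits. Week 72 is 16 February 2018, which is 47 days (6.7 weeks) late.

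**5. Patients whose T3 would fall after 31 December 2017.** The protocol states a target rate but no accrual pattern, so steady accrual is assumed. The low figure takes every patient as due at week 64, the high figure every patient as due at week 72.

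| Accrual assumed | Last inclusion | All at week 64 | All at week 72 |
|---|---|---|---|
| 10 per month (156/10 = 15.6 months) | about 18 July 2016 | 0 | 0 |
| 156 over 18 months (8.7 per month) | 30 September 2016 | 0 | 47/549 x 156 = 13 (9%) |
| 8 per month (156/8 = 19.5 months) | about 14 November 2016 | 36 days x 8/30.4 = about 10 | 92 days x 8/30.4 = about 24 |
| 156 over 21 months (7.4 per month) | 31 December 2016 | 83/640 x 156 = 20 (13%) | 139/640 x 156 = 34 (22%) |

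The last row follows the printed dates literally, but its rate lies below the 8-10 per month of Section 4.1. At the protocol's own rates the range is about 0 to 24.

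**The case against.** The strongest reply is that no data need be lost. Section 3 is a planning calendar, no passage orders collection to stop on 31 December 2017, Section 8.3 asks every patient for the 64-72 week measures, and Section 12.5 ends the study with the last patient's last visit. Under those rules T3 is collected and the date simply slips. This stands, and it makes the loss conditional. It does not make the printed dates consistent: it shows that the December 2017 date conflicts with Section 12.5 as well as with the T3 window.

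A reader might infer that late recruits lose the primary outcome altogether. The documents do not support that. T3 is not named as the sole primary time point. The BAI, EQ-5D, SF-36 and TiC-P are also taken at T0, T1 and T2, and Section 10.1 plans a multilevel model with repeated measurements that can use those data.

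A reader might also infer a large loss of power. Removing 22% of patients leaves about 61 per arm, and the Section 4.4 inputs then give z = 768/sqrt(2 x 2,944,000/61) - 1.96 = 0.51, or about 70% against the planned 80%. That figure requires the slowest accrual in the table, every patient on the 72-week schedule, and no use at all of T0-T2 data. It is a worst case, not an expectation. A cut-off by calendar date should also fall about equally on the two randomised arms, so its main cost would be precision.

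Finally, Section 4.1 adds recruitment locations "If after 6 months the number of included patients is less than 78 patients". That threshold needs 78/6 = 13 per month, whereas 8-10 per month gives 48-60. The figures do not match, but the rule only brings in sites early and biases no result. It merits a note and no more.

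**Conclusion.** The point holds as an error in the calendar. Section 3 contradicts itself: the follow-up end date is 12-20 weeks too early for a patient included at the end of December 2016, whose T3 falls between 24 March and 19 May 2018. That result needs only the printed dates and week numbers, comparing the end of one December with the end of the next. The recruitment periods in Sections 3 and 4.1 (about 21 and 18 months) also disagree, and the shorter one still leaves week 72 in February 2018.

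Loss of T3 data is conditional on collection actually stopping in December 2017. The number affected depends on an accrual pattern that the protocol does not fix: about 0 to 24 patients at 8-10 per month, and 20 to 34 if accrual is spread over the full 21 months. Those affected would lose the T3 SCID-I and the one-year costs and utilities, and keep T0-T2. The documents do not establish that any patient will in fact be lost, nor a particular fall in power.

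**What to change.** Set the end of follow-up in Section 3 at last inclusion plus 72 weeks, which is about May 2018 if inclusion runs to 31 December 2016. This agrees with the definition of end of study in Section 12.5. State one recruitment period in Sections 3 and 4.1.

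The cost is a change of date and up to about 5 more months (139 days) of online questionnaires and interviews that are already planned for each patient.

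Keeping December 2017 and closing inclusion by 14 August 2016 is less attractive. It leaves about 16.5 months, so 156/16.5 = about 9.5 inclusions per month would be needed, near the top of the stated target. The site-expansion rule need not change for this purpose.
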